## Abstract

**Introduction:**

The poor dietary habits and limited nutritional knowledge, particularly regarding indigenous vegetables and fruits (IVFs) among youth in southwest Nigeria, highlight the need for an integrated intervention approach. Integrating school-based gardening focused on IVFs with a nutrition education program delivered via WhatsApp combines experiential learning with digital tools.

**Methods and analysis:**

This is a non-randomized, mixed-methods study involving youths between 15 and 35 years who will participate in gardening activities and/or interactive nutrition education via WhatsApp. Participants will be provided technical support on growing IVFs, while nutrition education messaging via WhatsApp will include texts, images, and videos on nutrition and healthy eating behavior. Data at baseline will be collected on the study’s primary outcomes (awareness and interest in IVFs, household food security, nutritional knowledge and practices, fruits and vegetables intake, food safety self-efficacy, dietary diversity, anthropometric, and biomarker indicators). In contrast, data collection during the intervention and at post-intervention will include the study’s secondary outcomes (WhatsApp engagement, knowledge retention, and intervention acceptability). Mixed model regression and the Mann–Whitney U Test will be used to analyze the data collected. All analyses will be performed using IBM SPSS (version 23), and the statistical significance will be set at a *p*-value <0.05.

**Discussion:**

The present study will focus on the acceptability and feasibility of gardening and incorporate nutrition education delivered through WhatsApp to address the improvements in food security, dietary diversity, and other nutrition-related outcomes of youth in low-income countries. The expected outcomes include enhanced nutrition knowledge, healthier dietary habits, and greater acceptance of indigenous gardening. The result will support the development of effective, culturally acceptable strategies to promote healthy eating behavior among youths and influence future school-based nutrition programs in similar settings.

## Introduction

1

Youths, also known as “young adults,” are generally referred to as individuals in the developmental stage between childhood and adulthood (1). Globally, youths are a focus of public health and educational initiatives due to their potential for long-term impact on future health and well-being. Youths in Nigeria are all young people between the ages of 15 and 35 years (2). Nigeria has one of the largest youth populations in the world, with a median age of 18.1 years, and about 70% of the population is under 30 years of age (3). Previous cross-sectional studies conducted among Nigerian youths reported low nutritional knowledge and inadequate dietary habits (4), and high intake of starchy foods, cereals, legumes, and sugar with a variance of 11.5% (5). Furthermore, a recent systematic review study conducted among Nigerian youths reported a low intake of fruits and vegetables (6). In addition, cross-sectional studies have shown poor fruit and vegetable consumption among Nigerian youth. For instance, 32.4% of participants consumed infrequent fruits and vegetables intake, while only 9.7% of Nigerian youth met the recommended daily intake of fruits and vegetables (4). Furthermore, food insecurity rates among this age group have been reported to range between 15 and 48% (5, 7–10). The combination of these nutrition-related problems among this age group makes them an important target group for nutritional interventions.

The efficacy of nutrition interventions such as school-based feeding programs, community gardening, and nutrition education has been established in high-income countries (11). However, their efficacy among youths in low-middle-income countries such as Nigeria remains underexplored and less widely disseminated (12). Of these interventions, community gardening of IVFs presents a valuable opportunity to address food insecurity, promote diversity, preserve cultural food heritage, and improve dietary diversity and nutrition by providing locally available, nutrient-dense foods (13–16). Furthermore, the intervention may promote sustainability and local agriculture, reduce dependence on imported food, and deepen youth engagement with their local environment (17–19).

In recognizing the significance of indigenous food systems, the Task Force on Traditional and Indigenous Food Systems and Nutritional Sciences (IUNS) has emphasized the need for increased public awareness and further research into the benefits of IVFs (20). While many studies have highlighted low nutritional knowledge among youths and recommended an increase in IVF consumption and participation in vegetable gardening (21–24), most of these studies are cross-sectional, which prevents legitimate causal inferences and limits the prospects of studying the effectiveness of an intervention on nutrition outcomes in youth. This highlights the need for intervention research that promotes utilization and evaluates the effectiveness of IVFs on nutritional outcomes in youth. Moreover, previous studies have recommended implementing multiple interventions to improve nutrition and health outcomes (13, 25).

The integration of nutrition education in school-based IVFs gardening among youths holds promise for enhancing dietary habits and overall nutrition among the young population. Given the youth’s widespread use of mobile technology and its potential for delivering educational content, digital platforms could enhance these interventions. WhatsApp remains one of the easily accessible mobile phone messaging applications in Nigeria due to its broad usage among educators, community health workers, and students (26, 27). Various studies have proven that engaging youths in health education through WhatsApp is effective (28, 29). While a few studies have explored text messaging platforms for delivering nutrition education among Nigerian youths (30), none have yet integrated a WhatsApp-based nutrition education component into school-based IVF gardening programs. WhatsApp is widely adopted and offers advantages over traditional/face-to-face nutrition education. This may be because the former permits the inclusion of multimedia such as images, videos, audio, and document files, making it a more versatile and engaging tool for communication and education (31–33). Exploring the integration of digital platforms with hands-on experiential learning could present an opportunity to improve youth nutrition, particularly in areas with limited access to traditional interventions (34). Hence, this study will utilize WhatsApp as a digital learning tool to achieve the purpose of this study and will thereafter measure its impact on the target audience.

Specifically, the study will assess the impact of a school-based gardening program and WhatsApp-based nutrition education interventions on primary outcomes such as youths’ nutrition knowledge, fruit and vegetable-specific self-efficacy, food security, dietary diversity, anthropometric data, and skin carotenoid level. In this study, school-based gardening refers to structured gardening activities conducted within a school setting involving in-school and out-of-school youths residing in the same community as the school. These activities will engage participants in cultivating and harvesting vegetables to enhance agricultural skills, nutrition awareness, and healthy eating habits. This intervention will be guided by the Cognitive Theory of Multimedia Learning (CTML), Social Cognitive Theory (SCT), and Empowerment Theory (ET), all of which are described in details in the method section below. Furthermore, the study will also examine secondary outcomes such as the participants’ engagement, knowledge retention, and acceptability of the intervention.

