**Null Hypothesis:**
*There is no difference in nutrition knowledge, fruit and vegetable self-efficacy, dietary habits, and biochemical data between youth who receive the combination of school-based gardening of IVFs, and WhatsApp nutrition education compared to those who receive only school-based gardening of indigenous fruits and vegetables.*

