**Alternative Hypothesis:**
*There is a significant difference in nutrition knowledge, fruit and vegetable self-efficacy, dietary habits, and biochemical data between youth who receive the combination of school-based gardening of IVFs and WhatsApp nutrition education compared to those who receive only school-based gardening of indigenous fruits and vegetables.*

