### Overview and study design

2.2

This research design for the study is a non-randomized intervention study (quasi-experimental study design). A non-randomized study design was selected due to some feasibility constraints and logistical challenges. This includes challenges with schools meeting the inclusion criteria, such as the requirement for arable land, access to water facilities, and the presence of agricultural and nutrition teachers. Additionally, to align with policy priorities, ensure feasibility and sustained participation, sites will be selected in collaboration with state and local education authorities as well as community leaders, making random assignment impractical.

The study will be carried out in three Southwest Nigeria states which were selected from six states in the region: Ekiti, Osun, and Ogun. There will be two arms of intervention; one group will receive the school-based gardening of IVFs, and the second group will receive both school-based gardening of IVF and WhatsApp nutrition education. This means all participants will participate in the school-based gardening program of IVFs intervention. In addition, 50% (*n* = 130) of the participants will be selected for the nutrition education based on pre-selected criteria such as access to a web-supported phone and knowledge using social media like WhatsApp. Figure 1 summarizes the flow of activities in the study.

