#### Intervention plan

2.3.1

The school-based gardening component of the intervention, as illustrated in Figure 3, will kick off with a 2-day workshop among the targeted participants. This workshop will cover topics such as an introduction to IVF farming and seed production process, showcasing the best soil management practices, and nutrition and food safety education. The participants will also be introduced to digital tools in agriculture, particularly the use of virtual assistants to facilitate sustainable and efficient farming practices, streamlining workflows and revolutionizing how young farmers access expert-level advice virtually, at their convenience. They will also educate participants on agribusiness models for farming and farming-related commercial activities. After the workshop, the youths will be apportioned equal plots for farming on school farmland. Through the collaboration of the school authorities and communities, the out-of-school youths will also have plots to use on the school farmland. The participants will be provided with viable seeds and other farm equipment, such as drips, knapsacks, soil improvement materials etc. to facilitate their farming activities. This will give them the opportunity to utilize the knowledge of IVF farming learned during the workshop. The agricultural science teachers in the selected schools will supervise the new farmers’ work to support community ownership. Furthermore, participants will be provided with technical support to guide them on good soil health management using the climate-smart approach throughout the farming year. Technical support will be provided through both physical and virtual approaches. At the initial stage of transplanting, the technical support will be provided weekly and then fortnightly till the vegetables are well established. Specifically, support will be provided physically to farmers in rural or semi-urban areas who have limited access to internet facilities and electricity, ensuring compliance. In contrast, urban participants will receive support through both physical and virtual means. Leveraging virtual support technology will help save costs and reduce risks associated with city traffic.

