### Data analysis

2.5

Descriptive statistics such as frequency and percentages will be used for the socio-demographic characteristics (such as age, gender, student status, and household size) and other outcome of measures (such as knowledge retention, intervention acceptability, and nutrition-related outcomes) that are categorical variables, while mean and standard deviation will be used for the continuous variables. To assess the possibility of bias resulting from missing data, we will conduct sensitivity analyses by carrying out complete case analyses. As opined by Braun and Clarke, this will ensure the robustness and credibility of our result (61). Mixed model analyses will be used to assess the intervention’s impact on skin carotenoid levels, anthropometrics, and diet diversity score (62, 63). The mixed model analysis was chosen because it accounts for repeated measures and can effectively address issues related to missing data. In these analyses, the intervention arms will be treated as the fixed effect so that the measure’s outcome change between the school gardening-only participants and school gardening and nutrition education participants can be assessed by the coefficients or estimated using the least square means. Time and intervention arm will be included as both main effects and interaction effects. The random effect will account for variability variations between groups that might affect the response. We will control for participant’s age, gender, household size, youth status (out-of-school vs. in-school status), community, and state, by including them as covariates in the adjusted models of the mixed model analysis. Mann–Whitney U Test will be used to compare the acceptability of the nutrition intervention between the groups. The analysis will be performed using IBM SPSS (version 23), and the statistical significance will be set at *p*-value <0.05.

As described by Braun and Clarke (61), the participants’ audio (sessions responses) and video recordings (tasks) from WhatsApp engagement will be analyzed using thematic analysis. We will use inductive coding to deduce the theme directly from the data. The convergent mixed method will be used to integrate the qualitative analysis with the quantitative results. This ensures a proper understanding of how participants experienced and engaged with the intervention.

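### Every participant gardens and attends a workshop with nutrition teaching, so the study can estimate only what WhatsApp education adds, not the impact of gardening or of the combined package

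*Protocol article*

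**What the plan says.** **Claims.** The Introduction states that "the study will assess the impact of a school-based gardening program and WhatsApp-based nutrition education interventions on primary outcomes". Section 2.1 aims at the feasibility and effectiveness of gardening and WhatsApp education delivered in combination. Section 3 (Discussion) expects the study to be reference evidence that the strategies are effective. Section 3.2 builds its implications for school curricula and food insecurity on effectiveness having been demonstrated.

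**Design.** Section 2.2 describes two arms: "one group will receive the school-based gardening of IVFs, and the second group will receive both school-based gardening of IVF and WhatsApp nutrition education". It adds: "This means all participants will participate in the school-based gardening program of IVFs intervention". Half of the participants (130 of about 260) are selected for the WhatsApp course.

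**Shared workshop.** Section 2.3.1 says that the gardening component "will kick off with a 2-day workshop among the targeted participants", and its topics include "showcasing the best soil management practices, and nutrition and food safety education".

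**Hypotheses and analysis.** Both hypotheses in section 2.1 set the combined arm against "those who receive only school-based gardening of indigenous fruits and vegetables". Section 2.5 fits arm, time and their interaction, so that the "change between the school gardening-only participants and school gardening and nutrition education participants can be assessed by the coefficients".

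**The concern.** The claims and the design do not match in two ways.

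First, to attribute an impact to gardening, or to gardening and WhatsApp education together, one needs to know what would have happened without them. No group in this study supplies that. A gain seen in both arms could be reported as evidence that gardening works, or that the package works, when the design cannot separate it from other changes over the same period. The Introduction faults earlier cross-sectional work for not supporting causal conclusions; an uncontrolled before/after change does not support them either.

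Second, the comparator is named as gardening alone, but it also receives face-to-face nutrition and food safety teaching. A reader who takes the label literally could read a null difference as showing that nutrition education does not help. What was tested is whether WhatsApp delivery adds to teaching already given.

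**Working it through.** No figure in the plan bears on this point beyond the arm sizes, so the check is one of identification.

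**Inputs.** Gardening exposure: all participants, that is 260 of 260 (sections 2.2 and 2.2.1). WhatsApp exposure: 130 of 260 = 50% (section 2.2). Workshop: part of the gardening component, so given to both arms (section 2.3.1). Model terms: arm, time, arm by time (section 2.5).

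**Step 1: what each arm's change contains.** For any outcome, let
- t = the change that would have occurred anyway (season, secular trend, repeat testing),
- g = the effect of the gardening component, workshop included,
- w = the further effect of the WhatsApp course.

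Taking t and g as equal in the two arms:
- gardening arm: mean change = t + g
- combined arm: mean change = t + g + w

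**Step 2: what the model recovers.** The arm-by-time interaction is (t + g + w) − (t + g) = w. With the gardening arm as reference, the time coefficient is t + g. There are two observed changes and three unknowns. Only w is separated out.

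**Step 3: what the claims require.** The impact of gardening is g. The impact of the package is g + w, which equals the combined arm's change minus t. Both need t, and only a group without gardening could supply it. Reading the Introduction's sentence as a claim about the package therefore does not rescue it.

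**Step 4: whether t can be ignored.** Section 2.4.1.2 measures food insecurity over the past 4 weeks, and section 2.3.1 has support running through a farming year, so food access may shift with season. The knowledge and self-efficacy questions are asked at baseline and again after the intervention (Table 2). Nothing in the article justifies setting t to zero.

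**Step 5: what the comparator contains.** Setting the sections side by side:
- *Workshop, both arms (section 2.3.1):* nutrition and food safety, alongside farming, seed production, soil management, digital tools and agribusiness.
- *WhatsApp course, one arm (Table 1):* healthy eating (week 1), nutritional benefits (week 3), food safety (week 6), health benefits and disease prevention (week 7).
- *Primary outcomes:* nutritional knowledge and practices (section 2.4.1.3); food safety self-efficacy and practices (section 2.4.1.5).

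The same subjects appear in all three places. If the workshop already delivers a share s of an education effect E to both arms, the contrast is w = (1 − s)E. The article gives neither s nor E. In principle s can lie anywhere from 0 (no dilution) to 1 (nothing left to detect), so the loss cannot be sized.

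**Step 6: whether the plan acknowledges this.** Section 3.1 discusses selection bias, reduced internal validity, purposive sampling, self-report, dropout and generalisability. It mentions neither the missing no-gardening group nor the teaching given to the comparator.

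**The case against.** The operative parts of the plan already define the right contrast. The hypotheses, the arms and the model all concern the addition of WhatsApp education, and no hypothesis tests gardening by itself. The workshop is openly described as part of the gardening component, so the comparator label is loose rather than concealing. Content given to both arms is normal in an add-on design and does not bias the increment under test. Section 3.1 concedes reduced internal validity, and section 3.2 calls for a randomised longitudinal study.

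Most of this stands. It shows that the tested contrast is coherent; it does not support the wider claims in the Introduction, section 2.1, the Discussion and section 3.2. The conceded loss of internal validity is tied to non-random selection, which is a different problem from having no group without gardening.

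Three stronger readings are tempting and are not supported:
- *That the study loses a definite amount of power.* The article gives no effect size and no share for the workshop. The workshop is two days on many topics; the course is 10 weeks. The affected outcomes are also not those for which section 2.5 names the mixed model (skin carotenoids, anthropometrics, dietary diversity), and section 2.4.1.5 plans descriptive statistics for food safety self-efficacy.
- *That the observed contrast will be too small.* The arms are formed by phone access and digital literacy (sections 2.2 and 2.2.2), so the net direction of error is unknown.
- *That the nutrition session should be moved out of the workshop.* That would change the question from what WhatsApp adds to this programme to what any nutrition teaching adds.

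**Conclusion.** The point holds as a mismatch between claims and design. The identification result needs no numerical assumption: with gardening given to everyone, neither its impact nor that of the package has a controlled estimate. Reading the interaction as w additionally assumes that both arms share the same background change and the same response to gardening, which a non-randomised allocation does not secure.

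The comparator label is misleading rather than invalidating. Shared teaching may shrink the knowledge and food safety contrasts by an unknown amount. A null result there would mean that no added benefit of WhatsApp education was shown over gardening with workshop teaching, not that nutrition education is ineffective.

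**What to change.** 1. In the Introduction, section 2.1, section 3 and section 3.2, restate the aim and the expected conclusions as the added effect of WhatsApp nutrition education.
2. In section 2.5, state that before/after changes within arms are descriptive and are not evidence that gardening or the package is effective.
3. In both hypotheses, rewrite the comparator as *school-based gardening including workshop nutrition and food safety education*.
4. In section 3.1, add the absence of a no-gardening group as a limitation. Note there that teaching shared by both arms may reduce the knowledge and food safety contrasts, and how a null result should then be read.

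The cost is wording only. Arms, sample size, workshop, data collection and model are unchanged. What is given up is any claim that this study shows gardening, or the combined programme, to be effective.

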## Methods and analysis

2

### Study aim

2.1

This study aims to assess the feasibility and effectiveness of the delivery of nutrition interventions through combined school-based gardening of IVFs and WhatsApp nutrition education among the youth in Southwest Nigeria. Therefore, we hypothesize as follows:

